### Event Rates

The number of events should be recorded in detail and showing the event rate in 90 days of each treatment group in summary statement.

The event rate for each treatment group will be calculated as: the sum of number of event for all the patients / the sum of number of treatment periods for all the patients.

---

## 11.Study Population

### Disposition of Subjects

The number of subjects in each analysis population will be presented, subjects to be excluded from the Per Protocol population will be listed, and the total number of subjects attending each clinic visit will also be summarized by treatment group.

The number of subjects randomized, completed and prematurely withdrawn from the study will be presented for each treatment group. The primary reasons for withdrawal both prior to and post randomization will also be presented.

A data display listing and summary of deviations from the inclusion/exclusion criteria will be presented for all subjects who were either entered or randomized into the trial.

### Protocol Deviations

Subject data will be examined for evidence of protocol violators in order to assess how well the protocol was followed. Inclusion and exclusion criteria are detailed in the study protocol.

Subjects who commit protocol violations will be included in the FAS Population but excluded from the Per Protocol Population. These protocol violations will be shown in a listing. Subjects can either be full or partial protocol violators. A full protocol violator is completely excluded from the Per Protocol Population. A partial protocol violator has only some data excluded. For subjects who violated the protocol during the treatment period due to unpermitted changes in the medication or prohibited concurrent medication, the analysis will only use data recorded prior to the violation. For all violations which reference the treatment period, the treatment start date will be used as the reference date.

A listing of all possible protocol violators will be produced for clinical review. The final list of subjects who are protocol violators and are therefore excluded from

---

the Per-Protocol population will be agreed by the study team.

## Demographic and Baseline Characteristics

The following demographic information will be listed and summarized for subjects in each treatment group: age, sex, medical history, smoking history, weak-up stroke, randomization time, NIHSS score, intravenous thrombolysis, occlusion site, ipsilateral carotid artery occlusion, ASPECT score, infarct core volume and stroke subtype.

The continuous data followed normal distribution will be presented as mean and standard deviation, and the continuous data followed skewed distribution will be presented as median and interquartile range; categorical data will be presented as n(%). T-test or Wilcoxon rank sum test will be used for comparison between continuous variables, and Chi-squared tests, Fisher's exact test or Wilcoxon sum rank test will be used for comparison between categorical variables.

## 12.Efficacy Analyses

### Primary Efficacy Analysis

The primary endpoint is the modified Ranking scale at 90-day. FAS will be the primary population for efficacy analyses. PPS will be used as secondary population for the efficacy analyses. If the results in the PPS population are inconsistent with the FAS population, detailed analysis of the inconsistent results is required.

#### **Main Model**

Based on an intention-to-treat basis, an ordinal logistic regression model with site as a random effect will be used to calculate the common odds ratio between the two treatment groups. If the proportional odds assumption for ordinal logistic regression were not satisfied, the Wilcoxon-Mann-Whitney generalized odds ratio will be calculated using assumption-free ordinal analysis. All statistics will be two-sided with  $p < 0.046$  considered significant.

---

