**Figure 1. Study design: randomization algorithm**

### 3.2 Randomization

The random code will be generated by a central network randomization system with 24h real-time online service based on the simple randomization method. The researcher in each center will obtain the random code from the central network randomization system according to the enrollment order. Patients who meet the inclusion criteria and in whom written informed consent can be obtained, will be randomly assigned to the following treatment groups in a 1:1 ratio:

- BMM plus EVT group: patients will receive EVT with stent retriever or contact aspiration as first-line devices for thrombectomy plus BMM;
- BMM group: Patients will receive BMM alone.

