### **(2) Efficacy Analysis**

Primary efficacy endpoint: Based on an ITT basis, an ordinal logistic regression model is used to calculate the common odds ratio between the two treatment groups. All statistics will be two-sided with  $p < 0.046$  considered significant.

Secondary Efficacy Analyses: Endpoints including the 90-day mRS 0-2 will be analyzed using a binary logistic regression model. The infarct core volume change from baseline will be analyzed using student t-test or Wilcoxon rank sum test as appropriate.

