## Interactions with Subgroups

Summary tables will be produced for the predefined subgroups and interactions between treatment and these subgroups will be investigated, using an ordinal logistic regression model. A separate model will be used for each interaction to determine its significance. This will also be presented graphically on a forest plot.

The predefined subgroups including:

- Age ( $< 75$  vs.  $\geq 75$ )
- Weak-up stroke or not
- Last known well to randomization time ( $< 6h$  vs.  $\geq 6h$ )
- Stroke severity before randomization (NIHSS $<16$  vs. NIHSS $\geq 16$ )
- Intravenous thrombolysis or not
- Occlusion site (ICA vs. M1 segment)
- Ipsilateral carotid artery occlusion or not
- ASPECT score ( $< 3$  points vs.  $\geq 3$  points)
- Infarct core volume ( $< 70ml$  vs.  $\geq 70ml$ )
- Etiological stroke subtype (cardiac embolism vs. large artery atherosclerosis)

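### The primary ordinal model adjusts only for site: valid, but it gives up power and leaves chance imbalance uncorrected when prognostic baseline data are already collected

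*Supplement*

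**What the plan says.** **Primary model.** SAP v2.0, section 12, Main Model: "an ordinal logistic regression model with site as a random effect will be used to calculate the common odds ratio". No other term is named. If proportional odds fails, "the Wilcoxon-Mann-Whitney generalized odds ratio will be calculated using assumption-free ordinal analysis", again without covariates. Protocol V7.1, section 10.3.2, is barer still: "an ordinal logistic regression model is used to calculate the common odds ratio between the two treatment groups", with neither site nor covariates.

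**Secondary models.** The SAP's binary endpoints (mRS 0–2, mRS 0–3, early NIHSS response, recanalisation) use logistic models with a random site effect only.

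**Randomisation.** Protocol V7.1, section 3.2, describes a "24h real-time online service based on the simple randomization method". No stratification, blocking or minimisation is mentioned.

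**Baseline data.** SAP section 11 lists "age, sex, medical history, smoking history, weak-up stroke, randomization time, NIHSS score", then thrombolysis, occlusion site, ASPECTS, core volume and others. It plans between-group tests on these factors but does not say what follows if they differ. The subgroup factors drawn from this list enter the outcome analyses only through interaction models: "A separate model will be used for each interaction to determine its significance".

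**Other analyses of the primary endpoint.** These are LOCF and WCCF imputation and the per-protocol set. No covariate-adjusted analysis is planned, even as a sensitivity analysis.

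**The concern.** The sponsor's own text treats the unused variables as prognostic. The Chinese-language protocol (section 10.3.2, subgroup analysis) introduces the subgroup factors as ones that earlier studies consider may affect 90-day mRS. Protocol section 1.3 cites mRS 0–2 rates falling from 37.7% at ASPECTS 6 to 17.1% at ASPECTS 0–4. Section 1.1 explains an unusually low control-arm rate in pooled retrospective studies by imbalance in age, NIHSS, thrombolysis and time to admission.

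Two things are at stake. First, in a proportional-odds model, adjusting for strong pre-randomisation predictors gives a more powerful test of treatment at the same sample size. Second, under simple randomisation the realised arms will differ somewhat by chance on these factors. The site-only estimate carries that difference, and no planned analysis shows how much it matters. An adjustment added after a visible imbalance would be post hoc and open to challenge in an open-label trial.

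**Working it through.** **1. Reproduce the planned sample size.** Inputs from SAP section 6: control mRS 0–6 of 3/4/10/17/16/12/38%, common OR 1.73, two-sided alpha 0.046, power 0.90, 1:1 allocation, 10% attrition.

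Shifting the control distribution by OR 1.73 gives a treated distribution of about 5.1/6.4/14.6/21.0/16.2/10.5/26.2%. The Whitehead formula, with p̄ the mean of the two arms in each category, is

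N = 12 (z₁₋α/₂ + z₁₋β)² / [(ln OR)² (1 − Σ p̄ᵢ³)]

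- (1.995 + 1.282)² ≈ 10.74; (ln 1.73)² ≈ 0.300; 1 − Σ p̄ᵢ³ ≈ 0.952
- N = 450.3, so 451 evaluable, against 452 stated
- 451 / 0.9 = 501.1, so 502 enrolled, as stated
- power at 452 by the same formula: 0.901

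The figure reproduces. The formula has no covariate term.

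**2. Power with and without adjustment at N = 452.** The documents give no joint prognostic strength, so a range is assumed. Outcomes were simulated with simple randomisation and one standard-normal prognostic score of SD σ on the log-odds scale. Latent R² = σ² / (σ² + π²/3), so σ = 0.5, 0.75 and 1.0 give 7%, 15% and 23%. Cutpoints were set so that the marginal control distribution equals the plan's, and the average marginal log-OR was held at ln 1.73. Each run used 1,500 or 2,500 trials (Monte Carlo SE under 0.01). Site was left out.

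| Latent R² (assumed) | Power, unadjusted | Power, adjusted | Evaluable N for 90% power, adjusted | Conditional OR when marginal OR is 1.73 |
|---|---|---|---|---|
| 0 | 0.90 | 0.90 | – | 1.73 |
| 7% | 0.88–0.89 | about 0.91 | about 430–440 | 1.77 |
| 15% | 0.89 | 0.93–0.94 | about 400 | 1.81 |
| 23% | 0.88–0.89 | 0.95–0.96 | about 360 | 1.88 |

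**3. Type I error.** Under the null at nominal 0.046 (4,000 trials per setting), rejection was 0.042–0.049 unadjusted and 0.044–0.049 adjusted. Both analyses are valid.

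**4. Chance imbalance.** For one standardised score, the 95% range of the difference between arms is ±1.96 × √(4/452) = ±0.184 SD. In the null simulations the unadjusted log-OR moved by 0.467, 0.652 and 0.859 per SD of imbalance at R² 7%, 15% and 23%:

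- 0.184 × 0.467 = 0.086; OR factor 1.09
- 0.184 × 0.652 = 0.120; OR factor 1.13
- 0.184 × 0.859 = 0.158; OR factor 1.17

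**5. Which covariates are secure.** Age, NIHSS, NCCT-ASPECTS, time and occlusion site are all needed for eligibility or screening. Core volume is less certain. Protocol section 8.1 requires CTP or MRI, but the schedule in section 8.6 makes perfusion optional and calls CT+CTA+CTP only the preferred work-up. Patients with ASPECTS 3–5 enter without a core-volume limit (section 1.5).

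**The case against.** Nothing in the plan is wrong. The sample size reproduces, the site-only model holds its type I error, and its simulated power is within one or two points of 90%. Chance imbalance is already reflected in the test and the confidence interval. A site-only primary analysis is a legitimate choice. All of this stands.

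The size of the gain depends on the R² chosen. Eligibility narrows the prognostic range (age up to 80, pre-stroke mRS 0–1, NIHSS 6–30, restricted ASPECTS and core volume), and protocol section 1.2 notes poor interrater agreement for ASPECTS. With about 50 centres, the planned random site effect may already absorb some prognostic variance; this was not tested. These points stand too and argue for the lower part of the range.

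A reader might infer more than the documents support:

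- *That adjustment is the only protection, or that simple randomisation gives no balance.* Randomising about 500 patients balances covariates in expectation, and step 4 shows how small the residual range is.
- *That the site-only model underestimates the planned effect.* This would need 1.73 to be a covariate-conditional OR. SAP section 6 sets it beside a marginal control distribution, and the sample size follows from a formula without covariates. The difference between adjusted and unadjusted ORs is non-collapsibility, a change of target rather than bias.
- *That every listed covariate exists for every patient.* For core volume the documents do not secure this.

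**Conclusion.** The point holds as one of lost efficiency and uncorrected chance imbalance, not as an error or a bias. Over an assumed latent R² of 7–23%, prespecified adjustment adds about 3 to 7 points of power at 452 evaluable patients, and a chance imbalance at the edge of its 95% range would shift the unadjusted OR by a factor of 1.09 to 1.17. The direction is secure, and so are the documentary facts. The magnitude is conditional: it rests on the assumed R², on a single summary score standing in for the covariates, and on a simulation without the planned site effect. The change is worth making because the data are already collected and type I error is preserved.

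**What to change.** Before database lock and unblinding, amend SAP section 12:

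- Primary model: ordinal logistic with treatment, random site, age, baseline NIHSS, NCCT-ASPECTS and time from last known well to randomisation (all continuous), and occlusion site.
- Add baseline core volume only with a stated rule for missing values. Leave out variables fixed after randomisation, such as stroke subtype (classified at day 7 or discharge).
- Use the same covariates in the binary secondary models.
- Keep the site-only common OR as a supportive analysis.
- State that the adjusted OR is covariate-conditional and is expected to lie somewhat further from 1 than the marginal one.
- State that the Wilcoxon-Mann-Whitney fallback and the interim tests of proportions stay unadjusted.
- Align protocol section 10.3.2, which names neither site nor covariates.

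If the sponsor prefers to keep the site-only primary model, the minimum is to name this adjusted model as a sensitivity analysis.

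The cost is a text amendment, with no extra patients or data. The downsides are a conditional rather than marginal OR as the headline and a simple rule for missing covariates.

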## Interactions with Subgroups

Summary tables will be produced for the predefined subgroups and interactions between treatment and these subgroups will be investigated, using an ordinal logistic regression model. A separate model will be used for each interaction to determine its significance. This will also be presented graphically on a forest plot.

The predefined subgroups including:

- Age ( $< 75$  vs.  $\geq 75$ )
- Weak-up stroke or not
- Last known well to randomization time ( $< 6h$  vs.  $\geq 6h$ )
- Stroke severity before randomization (NIHSS $<16$  vs. NIHSS $\geq 16$ )
- Intravenous thrombolysis or not
- Occlusion site (ICA vs. M1 segment)
- Ipsilateral carotid artery occlusion or not
- ASPECT score ( $< 3$  points vs.  $\geq 3$  points)
- Infarct core volume ( $< 70ml$  vs.  $\geq 70ml$ )
- Etiological stroke subtype (cardiac embolism vs. large artery atherosclerosis)

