### **1.3 ASPECTS and infarct core volume selection**

A recent meta-analysis of 17 studies and 1378 patients reported mRS 0-2 was achieved by 37.7%, 33.3%, 22.1%, and 17.1% of patients with ASPECTS 6, 5, 4 and 0-4 respectively. The studies by Mourand et al. and Inoue et al. showed favorable outcomes in between 16% and 20% of patients with ASPECTS 0–3 after EVT. Another meta-analysis showed that ASPECT 0-2 favored MM instead of EVT. The benefit of EVT gradually declined with decreasing in ASPECTS, especially when ASPECTS < 3, because the infarct core volume was very large and there was less salvageable brain tissue, which might make EVT ineffective. Therefore, this study limited the ASPECTS of enrolled patients to 3-5.

There is some debate about whether “large core” should be defined as 50ml vs. 70ml on CTP. In ANGEL-ASPECT, the infarct core volume > 70 ml was defined as LICV. Similar to patients with ASPECTS 0-2, patients with excessive infarct core volume may also be less likely to benefit from EVT. Previous studies showed a lack of benefit if CTP-determined core volume exceeded 100 ml and 150 ml. Therefore, when patients were enrolled only based on the infarct core volume as assessed by CTP/MRI, this study limited the infarct core volume to 70 ml-100 ml.

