### **1.4 EVT time window for large infarct core volume**

Patients in the hyperacute phase of stroke showed increased ASPECTS lesion growth from imaging to recanalization, suggesting a benefit of faster recanalization in these patients. A meta-analysis by Cagnazzo et al. demonstrated that a shorter time from onset to reperfusion was associated with a higher probability of functional independence after EVT in patients with ASPECTS 0–6. The SELECT trial found that patients with LICV had a gradual decline in functional outcomes with prolonged treatment time, with a lower likelihood of benefit from EVT after 12 hours. This

suggested that for LICV patients, the earlier EVT may be more beneficial. However, a recent meta-analysis found that patients with LICV did not show a significant difference in outcomes among studies reporting <6 hours, <12 hours, and <24 hours for stroke to EVT time windows. This may be because most LICV patients presented in the early time window, reducing the power to detect the difference between early and late windows. The reason may also be that the efficacy of MM declines over time, thus preserving the efficacy of EVT. In this context, it is important to study whether EVT also benefits patients with LICV in the late time window, therefore the time window of ANGEL-ASPECT is 0-24 hours.

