### **1.5 ANGEL-ASPECT Trial design**

ANGEL-ASPECT trial is a PROBE study initiated by researchers to explore the effectiveness and safety of EVT in patients with anterior circulation large vessel occlusion with ASPECTS 3-5 or infarction core volume 70-100ml within 24 hours. ANGEL-ASPECT trial allows multiple imaging modalities to screen for LICV patients, but at the same time imposes certain limitations on the range of ASPECTS or infarct core volume. The main purpose was to reduce the risk of EVT while enrolling as many LICV patients as possible. The primary image inclusion criteria of ANGEL-ASPECT was NCCT-ASPECTS 3-5, and the infarct core volume 70 ml-100 ml was used as auxiliary inclusion criteria. Briefly, the inclusion criteria for LICV are: (1) If NCCT-ASPECTS is 3-5 and presentation is within 24 hours of onset, patients are enrolled without limitation of infarct core volume. (2) For NCCT-ASPECTS 0-2 and core infarction volume 70 ml-100 ml, patients are enrolled. (3) If NCCT-ASPECTS is >5 and between 6 to 24 hours from symptom onset, only patients with infarct core volume 70 ml-100 ml are enrolled.

Subgroup analysis will focus on age, LKW to randomization time, NIHSS score, IV thrombolysis, occlusion site, ASPECTS, infarct core volume, and stroke etiology.

ANGEL-ASPECT is the only randomized controlled trial conducted in China for LICV patients so far. The results of this trial will clarify whether EVT is effective and

safe in Chinese LICV patients.

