## **6. Sample size estimates**

In this study, a multicenter, open, randomized, parallel control design method was used. The primary measure of efficacy was mRS score at 90±7 days after enrollment (considered as ordered variable). According to the literature data and clinical experts' opinions, the parameters were set as follows: (1) The proportion of mRS score 0-6 in control group was 3%, 4%, 10%, 17%, 16%, 12% and 38%, respectively; (2) The average treatment effect of EVT improved the outcome with the common OR value for improvement of mRS reached 1.73; (3) Two Interim analysis were considered. Adjusted level  $\alpha=0.046$  (two-sided) and power  $1-\beta=0.90$ . (4) The sample size was allocated to the intervention group and the control group in a 1:1 ratio. Based on these parameters, the total sample size was 452. Considering 10% attrition rate, the final total sample size was 502 cases, 251 cases in each group.

Interim analysis will take place when 1/3 (168 cases) and 2/3 (336 cases) have completed 3-month follow-up. O'Brien-Fleming boundaries will be used at the interim analysis as follows:

There are no established techniques for the assessment of interim trial efficacy boundaries using an ordinal logistic regression model (proportional odds model). Instead, we will revert to a simple dichotomous analysis of the mRS score at 0-2 defined at 90 days from randomization. The Z-statistic for this analysis shall be derived from the normal approximation of the binomial distribution as an unadjusted two-sample test of proportions. For an RCT comparing two treatment groups with respect to a binary outcome and two interim analysis, corresponding significance levels based on O'Brien & Fleming boundary are two-sided 0.0002 (stage 1), 0.0123 (stage 2) and 0.046 (stage 3, final analysis).

With the result of interim analysis, DSMB will make the decision to continue or

---

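### The early-versus-late subgroup test ignores an entry route that exists only after 6 h, and the ≥70 ml stratum merges 70-100 ml with >100 ml

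*Supplement*

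**What the plan says.** SAP v2.0 section 12 (Interactions with Subgroups) lists ten subgroup factors. Three bear on entry: last known well to randomization (<6 h vs ≥6 h), ASPECTS (<3 vs ≥3) and infarct core volume (<70 ml vs ≥70 ml). On the modelling it says: "A separate model will be used for each interaction to determine its significance". It names no entry-route term and no restriction to a commonly eligible population. Protocol V7.1 section 10.3.2(4) uses the same three cuts.

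Protocol V7.1 sections 1.5, 4.1.3 and 5.1 define three routes into the trial:

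- ASPECTS 3-5, at 0-24 h; these "patients are enrolled without limitation of infarct core volume".
- ASPECTS 0-2, at 0-24 h, with core 70-100 ml.
- ASPECTS above 5, in the late window only: "If NCCT-ASPECTS is >5 and between 6 to 24 hours from symptom onset, only patients with infarct core volume 70 ml-100 ml are enrolled".

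Section 1.4 gives the reason for the 0-24 h window: "it is important to study whether EVT also benefits patients with LICV in the late time window". Section 1.3 explains the upper volume limit for patients who enter on core volume: "Previous studies showed a lack of benefit if CTP-determined core volume exceeded 100 ml and 150 ml".

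**The concern.** The early and late strata are selected by different rules. ASPECTS >5 patients can be present at ≥6 h and cannot be present at <6 h. If EVT works better or worse in them than in the rest, the <6 h vs ≥6 h contrast shows a difference that has nothing to do with time; it could equally mask a real one. With one factor per model, nothing in the plan separates the two explanations.

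The core-volume factor has a related gap. Patients above 100 ml can enter, but only through ASPECTS 3-5, and they fall into the same stratum as 70-100 ml. The protocol doubts benefit above 100 ml, yet no planned row estimates it. The contrast also mixes routes: every <70 ml patient has ASPECTS 3-5, whereas ≥70 ml holds all three routes.

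At stake is how two prespecified rows of the forest plot are interpreted, on questions the protocol itself raises in 1.3 and 1.4.

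**Working it through.** **Inputs from the documents (SAP v2.0 section 6).** "The proportion of mRS score 0-6 in control group was 3%, 4%, 10%, 17%, 16%, 12% and 38%, respectively"; "the common OR value for improvement of mRS reached 1.73"; significance levels "two-sided 0.0002 (stage 1), 0.0123 (stage 2) and 0.046 (stage 3, final analysis"; power 0.90; 1:1 allocation; 452 patients before attrition and 502 after.

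**Reproducing the plan's own figure.** Whitehead's proportional-odds formula is N = 12(z₁₋α/₂ + z₁₋β)² / [(ln OR)²(1 − Σp̄ᵢ³)], where p̄ᵢ is the mean of the control distribution and that distribution shifted by OR 1.73.

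- z = 1.995 (two-sided 0.046) and 1.282 (power 0.90)
- (ln 1.73)² = 0.3004; Σp̄ᵢ³ = 0.0475, so 1 − Σp̄ᵢ³ = 0.9525
- N = 12 × (3.277)² / (0.3004 × 0.9525) ≈ 450, against 452 stated
- 452 / 0.90 = 502.2, against 502 stated

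The sample size reproduces and is not in question. The same inputs serve below.

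**Assumptions not in the documents.** The documents give no route shares and no route-specific odds ratios. I assume OR 1.73 for ASPECTS ≤5 in both windows (no true time effect), the planned control distribution in every route, ASPECTS >5 as a share s of the late stratum, and OR r in that route.

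**Time contrast.** The late EVT distribution is (1 − s) × [control shifted by 1.73] + s × [control shifted by r]. A large-sample proportional-odds fit against control gives the OR the late row would show. The early row shows 1.73.

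| r in ASPECTS >5 | s = 20%: late OR (late/early ratio) | s = 40%: late OR (late/early ratio) |
|---|---|---|
| 1.0 | 1.55 (0.90) | 1.39 (0.80) |
| 3.0 | 1.93 (1.11) | 2.15 (1.24) |

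Widening s to 10-50%, and also letting the control-arm odds of a better outcome be doubled in the ASPECTS >5 route, gives late ORs of 1.31 to 2.27 and ratios of 0.76 to 1.31. Restricting to ASPECTS ≤5 returns the ratio to 1.00 by construction.

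**Core contrast.** With OR 1.73 at 70-100 ml and 1.0 above 100 ml, the pooled ≥70 ml OR is 1.55 when >100 ml makes up 20% of the stratum and 1.32 when it makes up 50%.

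**Could this create a significant interaction?** Var(ln OR) = 12 / [n(1 − Σp̄ᵢ³)]. With 452 analysed and split evenly, each stratum (n = 226) has SE 0.236, and the difference in ln OR has SE √2 × 0.236 = 0.334. The ratio detectable with 80% power is exp(2.8 × 0.334) ≈ 2.55. For a case-mix ratio of 0.80 or 1.24, the chance of p < 0.05 is about 10%. Over the wider range, with 30-70% of patients late, it is about 5-13%, against a nominal 5%.

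**The case against.** The strongest reply is that nothing here is biased. EVT versus BMM is randomised within each stratum, so the ≥6 h odds ratio is valid for the late population the trial enrols, which is arguably the question in protocol 1.4. Early and late patients differ in case mix in any trial, and one interaction model per factor is ordinary practice. That stands: the difficulty lies only in attributing an early/late difference to time.

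The cuts are also not arbitrary. Six hours, ASPECTS 3 and 70 ml are all entry boundaries, and 1.3 defines large core as above 70 ml. That is a reason to keep them, though not a reason to leave out 100 ml.

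A reader might infer that the ASPECTS 3 cut, too, pools the groups the protocol expects to differ. The documents do not support this. Section 1.3 expects the sharpest loss of benefit below 3, and the cut isolates exactly that group. It does join ASPECTS 3-5 with >5, but for those the protocol suggests only a gradual trend.

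The magnitudes rest on assumed shares. Section 1.5 calls core volume an auxiliary criterion, so the ASPECTS >5 share may be small. Finally, finer bands tested one factor at a time would themselves mix routes: 70-100 ml holds all three, whereas >100 ml is ASPECTS 3-5 only. That objection is sound, and the fix allows for it.

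**Conclusion.** The point holds as a limit on interpretation. As planned, a difference in EVT effect between <6 h and ≥6 h cannot be separated from the late-only ASPECTS >5 route, and the ≥70 ml row cannot say whether benefit holds at 70-100 ml, above 100 ml, or both. With assumed shares of 20-40% and route ORs of 1.0-3.0, case mix alone gives a late/early ratio of 0.80-1.24. With >100 ml at 20-50% of its stratum and OR 1.0 there, the ≥70 ml OR falls from 1.73 to 1.55-1.32. The true sizes cannot be fixed from the documents.

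A reader might infer that the primary result is affected, or that false-positive interactions are likely. Neither follows: the primary ordinal analysis uses no subgroup factor, and the interaction tests are too weak for this distortion to produce significance often. This is a low-cost improvement to secondary analyses.

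**What to change.** In SAP section 12, mirrored in protocol 10.3.2(4):

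1. Keep the planned cuts.
2. Run the <6 h vs ≥6 h interaction in patients with ASPECTS ≤5, who enter by the same rule in both windows, and show ASPECTS >5 as a separate row.
3. Report core volume as <70, 70-100 and >100 ml, and compare these bands within ASPECTS 3-5, so that entry route does not differ between them.
4. Label these analyses exploratory.

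The cost is a few lines of text; ASPECTS, core volume and onset time are already collected. The downside is small cells with wide intervals, mainly in the ASPECTS >5 and >100 ml rows. The restriction in step 2 removes the late-only route but not every difference between windows: core volume or thrombolysis use may still differ, and the report should say so.
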